#### Patients’ well-being

To check the effect of the intervention on the severity of depression, other psychiatric features, co-morbid symptoms, and general patient health, the following scales and questionnaires will be used:
MADRS scale (Montgomery-Asberg Depression Rating Scale) [47] for clinical assessment of depression severity will be administered by a well-trained psychiatrist. The MADRS is a 10-item scale that includes questions concerning apparent sadness, reported sadness, inner tension, reduced sleep, reduced appetite, concentration difficulties, lassitude, inability to feel, pessimistic thoughts, and suicidal thoughts. The assessment will always be performed by the same person blinded to the intervention type.BDI (Beck’s Depression Inventory [48]) for self-reporting measurement of the severity of depression. The BDI consists of 21 multiple-choice questions.SCL-90 (The Symptom Checklist-90 Questionnaire [49]) assesses the general intensity of psychopathological impairment. The SCL-90 is a self-reporting measurement tool that includes 90 items regarding the currently felt symptoms divided into nine subscales: somatization, obsessive-compulsive, interpersonal sensitivity, depression, anxiety, hostility, phobic anxiety, paranoid ideation, and psychoticism.PSS-10 (The Perceived Stress Scale [52]) includes 10 items and measures the self-reported perception of psychological stress in respondents by asking about their thoughts and feelings during the last month.CTQ Questionnaire (Childhood Trauma Questionnaire [53]) is used for the self-assessment of traumatic experiences which covers 28 items in total and consists of five subscales addressing: physical, emotional, and sexual abuse, and physical and emotional neglect.SF-36 Health Survey (The Short Form (36) Health Survey [50]) includes patients’ reports about their vitality, physical functioning, bodily pain, general health perceptions, physical role functioning, emotional role functioning, social role functioning, and mental health.The GSRS scale (The Gastrointestinal Symptoms Rating Scale [51]) is a self-administered questionnaire which assesses five symptom clusters (combined from 15 items) depicting: reflux, abdominal pain, indigestion, diarrhoea, and constipation experienced over the past week.

#### EEG

Electroencephalography (EEG) is a non-invasive method enabling the assessment of electrophysiological neural activity. Subjects participating in the study will sit with closed eyes throughout the EEG recording. The assessment will be carried out during the daytime, between 10:00 a.m. and 2:00 p.m. to ensure that participants will remain awake. The EEG recordings, after the initial calibration of the equipment, will last about 15 min so that after cleaning, we will have at least five minutes of pure electrophysiological recording available from each participant. To ensure study comparability and reproducibility of the study, a standard procedure will be conducted, with 19 electrodes placed according to the International 10–20 system [69, 70].

Oscillatory activity of the central nervous system may be analyzed in order to extract relevant information regarding the functioning of the brain. Resting-state EEG assesses spontaneous brain activity organized as a synchronized, or in the case of brain pathology, a desynchronized, system. The evaluation of task-free neural behavior allows a qualitative, clinical assessment of parameters such as the dominant frequency, the occurrence of pathological phenomena such as seizures, or abnormal brain response to stimulation. Digitized EEG recordings can be analyzed with advanced mathematical methods to assess the functional connectivity and organization of intrinsic neural networks. Functional connectivity (FC) refers to the process of neural synchronization that functionally integrates the cortical areas necessary to maintain consistent and effective brain activity. Based on various properties of the EEG signal, e.g. phase coupling, by applying non-linear mathematical methods (e.g. phase lag index, PLI) [71], it is possible to assess changes in the synchronization patterns as an effect of a given experimental intervention as well as those that reduce the inflammatory states within an organism. The most advanced analyses of the EEG signal concern the modelling of brain activity in the form of functional neural networks [72]. Network analysis enables the reconstruction of synchronized neural behavior as a global system of inter- and intra-cortical interactions, and not only as a given set of connections. Due to the implementation of the network approach, it is also possible to distinguish cortical areas, so-called hubs, that play a key role in neural integration. Their location and strength are critically important indicators of how the brain functions as an information processing system. Considering the above, we will apply the PLI as a functional connectivity measure and the network indicators adopted from graph theory such as centrality, network assortativity, metrics indicative of path length, and small-worldness [73].

Changes in FC have also been studied in patients with MDD [74, 75] and have shown that these EEG markers may have potential value as biomarkers. This concept created a new clinical possibility of considering MDD symptoms in connection with gut microbiota and structural and functional changes in the brain.

### Sampling

#### Blood collection

Venous blood will be collected by qualified nurses. The collection will be performed under conditions of fasting, upon overnight resting, in the morning, between 8:00 and 10:00 a.m., to minimize the effect of changes in daily cortisol production. To obtain serum, blood will be centrifuged at 1500×*g* for 10 min. Until analysis, the blood samples will be preserved in 2 mL Eppendorf tubes and frozen at a temperature of − 80 °C.

#### Stool collection

Participants will be asked to collect stool samples after overnight fasting to avoid the effect of food consumption on short-chain fatty acid synthesis. Each participant will receive detailed instructions describing the method for material collection. A plastic holder will be used to collect faeces into a sterilized screw-capped collection container. Participants will be asked to store the sample in a fridge and deliver the sample up to 24 h after collection to the clinic. The samples will be preserved in 2 mL Eppendorf tubes containing 600 μL DNA/RNA later solution (Zymo Research, Freiburg, Germany) to prevent the degradation processes and will be frozen at − 80 °C until the beginning of the microbiota analyses.

DNA extracted from the stool will be amplified using primers flanking the hypervariable region of the 16S rRNA gene. 16S amplicons will be sequenced using an Illumina MiSeq platform (Illumina Inc., San Diego, CA, USA) and the raw reads will be processed using the Mothur pipeline (version 1.39.5) [76]. The SILVA 132 rRNA database [77] will be used to assign taxonomy. To predict a microbial community metagenome and its functional potential based on the 16S data, the PICRUSt software package will be used [78].

An overview of the study design and assessments to be conducted during the study and their timing is presented in Fig. 1 (study design) and Table 1 (assessment point times and examined variables).

**Fig. 1 Fig1:**
[figure not shown]
Timeline of SANGUT STUDY visits. V0 – Screening visit; V1 – Baseline Visit; V2 – Visit 2; V3 – End of Study Visit

**Table 1 Tab1:** Schedule of study procedures

	Screening	Randomization	Intervention Period	End of the study
Visit Number	V0	V1	V2	V3
Visit time and Window	Day –7 to –1	Day 0	6 weeks ±3 days	12 weeks ±3 days
Informed consent	+			
Inclusion/exclusion criteria	+	+		
Somatic examination	+	+		
Neurological examination	+	+		
Socio-demographic characteristics	+			
Medical history	+			
Psychiatric history	+			
Depression symptoms severity	+	+	+	+
Stress level	+	+	+	+
Quality of life	+	+	+	+
Gastrointestinal symptoms	+	+	+	+
Dietary assessment	+	+	+	+
Physical activity	+	+	+	+
Anthropometric measures	+	+	+	+
Vital measures	+	+	+	+
Smoking status	+	+	+	+
Blood sample	+			+
Stool sample	+			+
Electroencephalography	+			+
Adverse events report		+	+	+

### Data management and analysis plan

#### Data analysis principles

To evaluate the efficacy of the intervention on the well-being of patients, the following changes from the baseline (V1) to the end of the study (V3) will be determined as primary outcomes:
The severity of depression symptoms:
MADRS total scoreBDI total scoreThe severity of psychopathological impairment:
SCL-90 total scoreThe quality of life:
SF-36 total scoreStress levels:
PSS-10 total score

To evaluate the effect of the intervention on physiological parameters [79], the following changes will be determined as secondary outcomes:
In serum, from the screening (V0) to the end of the study (V3), levels of:
proinflammatory biomarkers: hs-CRP, Il-6, Il-1beta, and TNF-alphagluten sensitivity biomarkers: anti-TG2 IgG antibodies and anti-AGA IgG/IgA antibodiesintestinal permeability biomarkers: I-FABP/FABP-2 and LBPmetabolism biomarkers: total cholesterol, LDL cholesterol, HDL cholesterol, TG, glucose, and insulinHPA axis biomarker: cortisolliver function biomarkers: ALT and ASTIn stool, from the baseline (V1) to the end of the study (V3):
taxonomic and functional analysis of gut bacterial communitySCFAs levelsBrain activity, from the baseline (V1) to the end of the study (V3):
EEG analysisGastrointestinal symptoms, from the baseline (V1) to the end of the study (V3):
GSRS scale.

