**Methods:**

A total of 120 outpatients will be equally allocated into one of four groups: (1) probiotic supplementation+gluten-free diet group (PRO-GFD), (2) placebo supplementation+ gluten-free diet group (PLA-GFD), (3) probiotic supplementation+ gluten containing diet group (PRO-GD), and (4) placebo supplementation+gluten containing diet group (PLA-GD). PRO groups will receive a mixture of psychobiotics (*Lactobacillus helveticus* R0052 and *Bifidobacterium longum* R0175), and GFD groups will follow a gluten-free diet. The intervention will last 12 weeks. The primary outcome measure is change in wellbeing, whereas the secondary outcome measures include physiological parameters.

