## Methods/design

### Aim and hypothesis

The main goal of the SANGUT study (a 12-week, randomized, double-blind, and placebo-controlled study) is to determine the effect of probiotic supplementation, a gluten-free diet, and their combination on the mental state, inflammatory markers, and gut permeability markers in adult patients with MDD. The primary hypothesis is that probiotic supplementation and/or a gluten-free diet will reduce the symptoms of depression, decrease levels of inflammatory markers, and favorably affect the integrity of the intestinal mucosal barrier.

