### Statistical analysis

Statistical analysis will be performed according to the E9 Statistical Principles for Clinical Trials [80]. For quantitative outcomes, the between-group comparisons will be performed using the ANOVA or Kruskal-Wallis rank-based nonparametric test depending on the data distribution followed by appropriate post-hoc tests. The qualitative outcomes will be compared using the Chi-square test. Longitudinal data will be analyzed with either repeated measures of ANOVA or aligned rank-transform ANOVA, depending on the data distribution, or McNemar’s test.

The analysis of the gut microbial community will include alpha diversity, beta diversity, ordination techniques (a principal coordinate analysis), and taxonomic and functional differences. Alpha diversity will be measured by means of the Chao1 (richness) and Shannon (richness and evenness) indices. All indices will be determined using originally observed count data (without data pre-processing) and comparison within the groups (V0–V3) and between the groups at the end of the study (at V3) using the non-parametric Wilcoxon signed-rank test or Mann-Whitney (or Kruskal-Wallis) test, respectively. Beta-diversity will be measured by means of the Bray-Curtis dissimilarity metric and the weighted UniFrac distance metric. Beta-diversity analysis will be preceded by the removal of rare species and normalization to account for unequal library sizes. The between-group differences in gut microbial composition will be visualized using principal coordinate analysis based on the Bray-Curtis dissimilarity and UniFrac distances. The permutational multivariate analysis of variance (PERMANOVA) will be conducted on the Bray-Curtis and weighted UniFrac dissimilarity matrices to assess the group-level (at V3) differences. Taxonomic differential abundance will be tested by comparing the fractional abundances. The analysis of alpha and beta diversity, ordination analysis, and taxonomic differential abundance will be conducted using the R (version 3.5.1) package Phyloseq [81]. The PERMANOVA+ add-on package of PRIMER 7 (version 7.0.13) will be used as analysis tools to compare beta diversity. To predict the metagenome functional content using the output of the 16S rRNA analysis pipeline, the software package PICRUSt will be used. Functional abundance differences will be analyzed and visualized using STAMP [82]. To account for multiple testing, FDR-adjusted *p* values (q values) will be reported.

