To the best of our knowledge, this will be the first intervention study assessing the efficacy of both probiotic supplementation and a gluten-free diet and comparing the effect of both interventions and their combination in MDD patients. The protocol and the outline were developed by a multidisciplinary researcher team. The methodology employed in the study benefited greatly from our diverse set of knowledge, experience and perspectives. Considering the highly rigoristic selection criteria, the participant group is relatively large. Rigorous procedures established for this trial will be followed by well-trained researchers to ensure that research will be conducted in accordance with standards of best practice. The measurements listed above will be introduced to reduce the potential bias related to confounding variables (e.g. smoking, physical activity, and diet).

There may be some possible limitations in the design of the study:

First, the impossibility of blinding the diet is a factor that could affect assessment of both the participant and investigator. For this reason, the researcher evaluating the severity of symptoms will not be informed as to whether the patient will be allocated to the GFD or GD arm of intervention.

Second, the lack of motivation is a symptom commonly experienced by MDD patients and could contribute to the non-attendance at the study visits, incomplete implementation of the intervention, or failure to complete the intervention.

Third, patients in the GFD groups receiving dietary advice might try to introduce other changes in food consumption (e.g. reduce the food portion size and/or consume more vegetables and fruits). Therefore, health improvement may not be specific to the implemented gluten-free diet.

Finally, recall bias in self-reporting is another potential confounder of the study. However, dietary consultation and food intake assessment during the study period should minimize the likelihood of its occurrence.

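### Five unranked scales are all primary while the power statement covers one null hypothesis, the reach of the only multiplicity sentence is unclear, and the primary hypothesis does not match the outcome list

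*Protocol article*

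**What the plan says.** **Outcomes.** Data analysis principles states that "the following changes from the baseline (V1) to the end of the study (V3) will be determined as primary outcomes". The list holds the MADRS, BDI, SCL-90, SF-36 and PSS-10 total scores. None is ranked first, and nothing says how many must succeed. The abstract does not settle it: "The primary outcome measure is change in wellbeing".

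**Hypothesis.** Aim and hypothesis reads: "The primary hypothesis is that probiotic supplementation and/or a gluten-free diet will reduce the symptoms of depression, decrease levels of inflammatory markers". It goes on to the intestinal barrier. Inflammatory and permeability markers are secondary in Data analysis principles. Psychopathology, quality of life and stress are primary there but do not appear in the hypothesis.

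**Power.** Sample size calculation gives about 81% with 116 patients in total, for one null hypothesis of no difference between the groups.

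**Tests.** For quantitative outcomes, "the between-group comparisons will be performed using the ANOVA or Kruskal-Wallis rank-based nonparametric test depending on the data distribution", with post-hoc tests after it. "Longitudinal data will be analyzed with either repeated measures of ANOVA or aligned rank-transform ANOVA". No adjustment across scales is mentioned in that paragraph. The sentence that "FDR-adjusted *p* values (q values) will be reported" ends the next paragraph, which is about the gut microbial community, directly after the PICRUSt and STAMP steps.

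**Blinding.** The Discussion concedes "the impossibility of blinding the diet is a factor that could affect assessment of both the participant and investigator". Its remedy is a symptom rater who is not told the diet arm. Under Patients' well-being such a rater is described for MADRS only; the other four primary scales are described as patient-reported.

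**The concern.** With five primary outcomes of equal standing and no decision rule, the document does not say what would make the trial positive. A significant result on whichever scale happens to succeed could be reported as a primary finding. The power statement does not allow for this, because it describes one test.

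The mismatch between hypothesis and outcome list adds to the uncertainty. A result on inflammation would bear on the stated primary hypothesis but come from a secondary outcome. A result on stress would be a primary outcome with no stated hypothesis behind it.

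For the diet question there is a further problem. If only one scale succeeds, it is likely to be one that the blinded rater does not protect, since four of the five are of that kind. A primary claim for the gluten-free diet could then rest wholly on reports from patients who know what they were assigned to eat.

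**Working it through.** **Inputs from the protocol article**
- Five primary scales (Data analysis principles).
- Four equal groups (Randomization) and 116 patients for power (Sample size calculation), so 116 / 4 = 29 per group.
- An omnibus test over four groups, then post-hoc tests (Statistical analysis).

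**Assumptions, because the article does not give them**
- Alpha 0.05 per test.
- A common correlation between scales of 0 to 0.9.
- No true effect on any scale, unless stated otherwise.
- For the power check: medium effect taken as Cohen f = 0.25, m = 4 measurements (V0 to V3), within-patient correlation 0.5.

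**Step 1: the stated power.** For the between-groups factor in a repeated-measures ANOVA, lambda = N f² m / (1 + (m − 1) rho) = 116 × 0.0625 × 4 / (1 + 3 × 0.5) = 29 / 2.5 = 11.6. With 3 and 112 degrees of freedom at alpha 0.05, power is 0.812. So the stated 81% is what one test at an unsplit 0.05 gives under these settings. The settings were found by matching the figure. Others give other values, for example 0.783 with three measurements at correlation 0.5, or 0.761 with four at 0.6.

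**Step 2: five independent tests.** 1 − 0.95^5 = 1 − 0.774 = 0.226.

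**Step 3: five correlated omnibus tests.** Simulation of 40,000 trials, 4 groups of 29, five equally correlated scales, one four-group F test per scale:

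| Correlation between scales | At least one p < 0.05 |
|---|---|
| 0 | 22.7% |
| 0.5 | 18.6% |
| 0.8 | 13.4% |
| 0.9 | 11.0% |

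**Step 4: if the FDR sentence covers the five scales.** Benjamini-Hochberg at 0.05 on the same five F tests (60,000 trials) gives at least one false result in 5.0%, 4.7%, 3.8% and 3.4% of trials at correlations 0, 0.5, 0.8 and 0.9, when no scale has an effect. When three scales have a true effect (3.5 standard errors, two-sided z tests, 400,000 runs) and two have none, the chance of a false claim on one of those two is 7.5%, 6.3% and 4.6% at correlations 0, 0.5 and 0.8. FDR therefore handles the case of no effect anywhere but does not guarantee 5% in general.

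**Step 5: hypothesis against outcome list**

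| Construct | In primary hypothesis | Rank in Data analysis principles |
|---|---|---|
| Depression severity (MADRS, BDI) | yes | primary |
| Psychopathology (SCL-90) | no | primary |
| Quality of life (SF-36) | no | primary |
| Stress (PSS-10) | no | primary |
| Inflammatory markers | yes | secondary |
| Intestinal barrier markers | yes | secondary |

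Only one of the six rows agrees.

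**The case against.** The strongest defence is that this is a condensed article. It states neither an alpha nor a success rule, and it nowhere says that one scale out of five is enough. Adjustment across outcomes is commonly left to a statistical analysis plan, which is not shown. The FDR sentence stands under the general heading Statistical analysis and is not expressly limited to the microbiota. If it covers the primary scales, the inflation under no effect disappears (Step 4).

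Much of this stands. It rules out saying flatly that there is no error control, and it makes the percentages conditional. It does not remove the point. The number and rank of the primary outcomes, the wording of the primary hypothesis and the single-hypothesis power statement are all fixed in this document. An analysis plan could not make hypothesis and outcome list agree without overriding one of them.

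A reader might infer more than the text supports:
- **That the hypothesis lets any scale win.** Its and/or joins the two interventions; the outcome domains are joined by and.
- **That every question (probiotic, diet, combination) on every scale is a separate ungated test.** The plan is an omnibus test followed by post-hoc tests. If post-hoc tests are run only after a significant omnibus test, the chance of any false result when nothing works cannot exceed the figures in Step 3.
- **That the plan's power falls to a particular lower figure.** The article gives no formula, effect-size value or alpha, and the matching settings in Step 1 are assumed. A loss would arise only if alpha were split, which the article does not propose.
- **That all self-reported results are unblinded.** The placebo capsule is described as indistinguishable, so the probiotic comparison is blinded on every scale. The open diet is also disclosed as a limitation.

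**Conclusion.** The concern holds in this form. The document fixes five primary outcomes of equal rank, powers one null hypothesis, and leaves it at best unclear whether its only multiplicity sentence reaches them. Taken as five separate tests, the chance of at least one false omnibus result is about 11% to 23%, against 5% for a single named scale. This rests on an assumed alpha of 0.05, an assumed correlation of 0.9 down to 0, and no true effect. The upper end needs independent scales, which is unlikely when MADRS and BDI measure the same construct. If FDR is meant to apply, the figure is about 3 to 5% under the same null, but it can exceed 5% when some scales respond and others do not.

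Two parts do not depend on any assumption. The primary hypothesis and the primary outcome list disagree in both directions. And for the diet comparison only MADRS has a described blinded rater, so a diet claim on any of the other four primary scales would be an open-label result.

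**What to change.** - Name the change in MADRS total score from V1 to V3 as the single primary outcome. It is the only one of the five with a described blinded rater, and a single outcome keeps the one-test basis of the stated power.
- Move BDI, SCL-90, SF-36 and PSS-10 to secondary, tested under Holm or in a fixed order after MADRS.
- As a minimum alternative, keep the five as primary, state a family-wise procedure over them, and restate the power at the adjusted level.
- State which analyses the FDR sentence covers.
- Align Aim and hypothesis with Data analysis principles: limit the primary hypothesis to depression severity and state inflammation and barrier integrity as secondary hypotheses.
- Report diet effects on self-reported scales as open-label results.

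The single-primary option costs protocol text and a registry update, with no added patients or visits. The downside is that four scales lose primary status.

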### Sample size calculation

Based on the results of other studies evaluating probiotic strains that will be used in the present study, we assume that the mean effect of intervention will be of a medium size. As the primary outcomes will be repeatedly measured and four groups of patients will be entering the trial, there will be an approximately 81% probability of correctly rejecting the null hypothesis of no difference between the study groups with a total of 116 patients.

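### Five unranked primary outcomes share one single-test power figure, and no error control is clearly tied to them: the chance of at least one false positive primary result is about 15–23% at 5% per scale

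*Protocol article*

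**What the plan says.** Under Data analysis principles, the article states that "the following changes from the baseline (V1) to the end of the study (V3) will be determined as primary outcomes". The list that follows contains five total scores: MADRS and BDI (depression severity), SCL-90 (psychopathology), SF-36 (quality of life) and PSS-10 (stress). They stand side by side. The abstract summarises them under one heading: "The primary outcome measure is change in wellbeing".

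Sample size calculation refers to the primary outcomes in the plural but gives one figure: "approximately 81% probability of correctly rejecting the null hypothesis of no difference between the study groups with a total of 116 patients". It gives no significance level. The effect is described only in words: "we assume that the mean effect of intervention will be of a medium size".

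Statistical analysis sets a four-group ANOVA or Kruskal-Wallis test for quantitative outcomes, followed by post-hoc tests whose method is not named. The one sentence on multiplicity begins "To account for multiple testing, FDR-adjusted". It comes at the end of the microbiome paragraph, directly after the functional-abundance analysis, and does not say which tests it covers.

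**The concern.** With five primary outcomes and no rule joining them, the text does not say what result makes the trial positive. One scale below the significance threshold, all five below it, or a particular one would each be a defensible reading. These readings differ greatly in false positive rate and in power, and one power figure cannot describe them all.

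The risk is that a result on whichever scale happens to reach significance is reported as a primary finding, with an error rate well above the nominal level. The stated power, meanwhile, belongs to a single test that the article does not identify.

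**Working it through.** **Inputs from the article.** Five primary scores; four groups allocated equally; total N = 116 (29 per group) for the power statement and 120 planned; stated power about 81%; four visits (V0 to V3); omnibus test followed by post-hoc tests.

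**Assumptions, because the article gives no figure.** Significance level 0.05; a medium effect taken as Cohen f = 0.25; correlation between repeated measurements ρ = 0.5; correlation r between scales from 0 to 0.8.

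**Step 1: reproduce the 81%.** For the between-groups factor in a repeated-measures ANOVA with m measurements, the noncentrality is λ = N·m·f² / (1 + (m − 1)ρ), with (3, N − 4) degrees of freedom.
- With N = 116 and m = 4: λ = 116 × 4 × 0.0625 / 2.5 = 11.6. Power at 0.05 is 0.812, which matches. 116 is also the smallest multiple of four that reaches 80%.
- Other settings at N = 116 do not match: m = 3 gives 0.783, m = 2 gives 0.729, a one-way ANOVA gives 0.590, and a group-by-time interaction gives more than 0.97.

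So the figure behaves as one between-groups test at an uncorrected 0.05.

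**Step 2: chance of at least one false positive among five omnibus tests.** If the scales are independent, this is 1 − 0.95⁵ = 22.6%. The table gives simulated values (20,000 trials, 4 × 29 patients, five equally correlated normal outcomes, no true effect).

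| r between scales | 0 | 0.3 | 0.5 | 0.7 | 0.8 |
|---|---|---|---|---|---|
| Any of five omnibus tests < 0.05 | 22.9% | 21.2% | 18.9% | 15.7% | 12.9% |
| Any active-versus-control post-hoc test < 0.05, run only after a significant omnibus test | 18.8% | 17.4% | 15.8% | 13.1% | 10.8% |
| Any post-hoc test, Bonferroni over the three comparisons within each scale | 20.3% | 18.8% | 17.0% | 14.1% | 11.8% |
| Benjamini-Hochberg at 5% over the five omnibus tests | 5.1% | 4.9% | 4.9% | 4.1% | 3.7% |

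Gating the post-hoc tests, or adjusting them within a scale, leaves about 13–20% for r from 0.7 to 0. Neither acts across the five scales.

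**Step 3: power under explicit rules**, with the λ that gives 81%.
- One named scale at 0.05: 81%.
- One named scale at the Bonferroni level 0.05 / 5 = 0.01: 60.1% at N = 116, and 62.3% at N = 120 (λ = 12). About 164 patients (λ = 16.4) would bring it back to 81%.
- All five required at 0.05, with an effect of this size on every scale: 0.812⁵ = 35% if independent, about 52% at r = 0.5 and 60% at r = 0.7.
- At least one of five at 0.01 (the first Holm step), with an effect on every scale: 1 − (1 − 0.601)⁵ = 99% if independent, about 91% at r = 0.5, 84% at r = 0.7 and 80% at r = 0.8.

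**The case against.** The strongest reply is that this is a condensed article. Several primary outcomes are permissible, and the adjustment and success rule may sit in an analysis plan that is not shown. That stands as far as the method of adjustment goes. It does not cover what the article itself fixes, which is a set of five primaries and one power figure. A later plan could add a correction, but the 81% would then need to be matched to the rule adopted.

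The second reply is that a multiplicity statement does exist. If it covered the five omnibus tests, the false positive rate with no true effect anywhere would be about 4–5%. That is correct, and it is why one cannot say there is no error control at all. But the sentence's position points to the microbiome analyses. False-discovery-rate control also does not bound the chance of a false claim when some scales truly respond and others do not.

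A reader might infer four stronger things that the documents do not support.
- *An and/or success rule over the scales.* In Aim and hypothesis, "The primary hypothesis is that probiotic supplementation and/or a gluten-free diet will reduce the symptoms of depression", the and/or joins the two interventions. The effects that follow are joined by and.
- *A false positive rate of 34–48%.* This arises from three active-versus-control comparisons per scale, ungated and unadjusted. Statistical analysis orders an omnibus test first.
- *That 81% fails under every error-controlling rule.* A fixed testing sequence keeps it for the first scale. Holm with any one scale sufficing gives about 80–99% if all five respond.
- *That the abstract is wrong.* Well-being is the umbrella term the article itself uses for these scales.

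**Conclusion.** The point holds in this limited form: five co-listed primary outcomes, no stated decision rule, no error control clearly attached to them, and a power figure that fits one uncorrected test. At 5% per scale the chance of at least one false positive primary result is about 15–23% for between-scale correlations from 0.7 to 0, or roughly three to four and a half times nominal (13% at 0.8).

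The size rests on an assumed 5% level, no true effect on any scale, and an assumed range of correlations. The 60% and 35–60% power figures rest on f = 0.25, four measurements and ρ = 0.5. That combination reproduces the stated 81% but is not given in the article. The reconstructed test averages over all visits and is not itself a test of the V1-to-V3 change. It therefore shows how the figure was probably obtained and how it moves with the significance level, and does not validate it for that change.

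**What to change.** Preferred: name MADRS total score, change from V1 to V3, as the single primary outcome. It is the scale used for entry (Study population) and is scored by a psychiatrist blinded to the intervention type (Patients' well-being). The other four are patient-reported, and the Discussion concedes that diet cannot be blinded. With one primary tested at a stated 0.05, multiplicity takes nothing from the 81%. Make BDI, SCL-90, SF-36 and PSS-10 secondary, tested in a fixed order or with Holm, and name MADRS in the abstract's outcome line.

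Alternative: keep five primaries, state whether one or all must be positive, apply Holm across them where any one suffices, and restate power for that rule.

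In both cases, state the significance level and say which tests the false-discovery-rate sentence covers.

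Cost: wording in the protocol, and in the registration if it lists the five as primary. No new patients or data are needed. The downside is that four scales lose primary status or, if all five stay, that the stated power changes.
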